## Methods

### Experimental Design Overview and Aims

This study was conducted as a cluster-randomized effectiveness study in which primary care teams, within sites, were randomized to one of two conditions: proactive case identification followed by adherence counseling and medication management delivered by a clinical pharmacist trained in behavioral counseling approaches (motivational interviewing) or usual care. This study involves the collection and analysis of both quantitative and qualitative data (the latter primarily at VA sites) during a 14 month intervention period. Qualitative data were also collected at VA sites before the intervention to assess how to make the intervention most effective and after the intervention to evaluate the implementation process, attainment, and sustainability.

Randomization occurred at the team level to evaluate the real-world effectiveness of pharmacist-team interactions rather than just the efficacy of pharmacist interactions with selected patients and to minimize cross-over contamination. At three of the study sites, existing primary care teams were randomly assigned to two intervention teams and two usual care (control) teams. At the fourth study site, the existing primary care teams were randomized to one intervention and one usual care team. At the fifth site, where a true team structure didn't exist, two artificial teams were constructed and randomized to one intervention and one usual care team, for a total of 8 intervention and 8 control teams. Each team consisted of primary care providers, their staff, and patients. All sites were recruited before randomization and then block randomized by site in order to minimize differences in baseline characteristics due to site. Randomization was done by random number generator. Thus allocation concealment was achieved at the cluster level.

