### Outcome Measures

#### Primary Outcome

The primary outcome is the relative change in systolic blood pressure measurements over time as recorded at the point of care in VA and KP electronic databases (excluding blood pressures measured by the AIM pharmacists). As this is an effectiveness study, change in each group will be assessed by the comparison of a precision weighted average of the values obtained during routine outpatient clinical practice in 6 month windows preceding and following the intervention period. The 6 month windows placed on either side of the intervention period ensure that a positive finding of the study would suggest a persistent effect on BP and not just a transient effect during the intervention. Secondary outcomes are described in Table 1.

**Table 1 T1:** Secondary Outcomes

*Description*	*Time period*	*Planned analyses*
*A1c *Change in the percentage of eligible patients with an average A1c > 8%	6 months preceding and following intervention period	Hierarchical logistic regression with a dichotomous dependent variable indicating whether each patient on a team is in control or not in each of the baseline and post intervention periods. The cluster identifier is the team, and the analysis will be stratified by site with fixed site effects. Using an analogous model, the primary hypothesis will be tested by examining the interaction between the treatment group variable and the time period variable at the laboratory measurement level.

*LDL *Change in the percentage of eligible patients with an LDL-c >100 mg/dl	6 months preceding and following intervention period	[See A1c]

*Medication Adherence *Change in rates of poor adherence (>20% gap days)	12 months preceding and following intervention period	Regression with a logit link and binomial error term

*Medication Intensification *Count of medication intensification events for BP, lipid, and hypoglycemic therapy [intensification event defined as 1) an increase in the dose of at least one medication or 2) the addition of another medication, or both]	During intervention period	Negative binomial regression

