It was felt to be important to use blood pressures obtained through routine care to assess the impact of the intervention, again to maintain comparability to the control group who would otherwise have to be invited for special visits to measure their baseline and post-intervention blood pressures. As the number of measurements may vary and thus provide more or less precise estimates of the two endpoints, it is not possible to simply construct a difference between the average pre- and post BPs. We will use all data when multiple measurements allow us to estimate a change in BP more precisely as well as those observations in which only 1 measurement occurs in each period with weighting to reflect the varying precision of the estimates.

A three-level multilevel model will allow us to do this with the multiple individual BP measurements (both pre and post intervention) at level 1 nested within patient identifier at level 2 and team at level 3. An indicator variable will represent whether the BP is from the pre or post period coded so that the coefficient estimates the change in mean BP for the control group. The coefficient of an indicator variable representing treatment teams will estimate the mean BP difference between treatment and controls in the baseline period. The primary hypothesis will be tested by an interaction term between the treatment group indicator and the time period indicator variables. The multilevel structure of the model will account for the varying precision with which the BP endpoints are estimated and the clustering of patients within teams. Site will be included as a fixed variable.

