#### Sample Size

Our perspective focusing on effectiveness had a substantial impact on our sample size requirements and subsequent design decisions. Our pharmacist intervention was designed to be integrated into existing provider teams, especially with the need for substantial trust between the providers and pharmacist in order to allow the pharmacists to make medication adjustments and the ability to easily consult with providers should discussion about those adjustments be required. Thus, we needed to randomize provider teams to intervention vs. control rather than individuals.

A cluster randomized trial requires substantially larger sample sizes than a simple RCT, contingent on the amount of clustering of the dependent variable by team as measured by the intraclass correlation coefficient (ICC). We attempted to ameliorate the effect of clustering in several ways. First, the focus on difference in blood pressure as opposed to post intervention blood pressure removes much of the potential systematic patient differences in blood pressure across teams. Furthermore, we decided to randomize teams within site, essentially moving all of the between site variation in blood pressure decline to a stratification variable that can be adjusted for in the analysis. Prior work suggests that ICCs for blood pressure are well under 0.02 for physician teams, much less than for sites of care [44-48]. Furthermore, focusing on the change in blood pressure rather than a cross sectional blood pressure measurement will reduce this clustering even further.

Our sample size calculations demonstrated that with an average of 275 participants contacted (or attempted to be contacted) per team, we could detect a 4.4 mmHg difference with a power 0.8 with only 2 observed blood pressures per person in each of pre and post intervention measurement windows, under the most pessimistic assumptions of an ICC of 0.02.

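### As described, the primary model names no team-level variation in BP change, so the treatment-by-period test may omit the clustering that the sample size appears to include

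*Protocol article*

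**What the plan says.** The section Design Issues for analysis and sample size calculations sets out the primary model. Individual BP readings, pre and post, are level 1, "nested within patient identifier at level 2 and team at level 3". The fixed terms are a pre/post indicator, a treatment indicator and their product. "The primary hypothesis will be tested by an interaction term between the treatment group indicator and the time period indicator variables". Of the multilevel structure, the section says that it "will account for the varying precision with which the BP endpoints are estimated and the clustering of patients within teams". It ends: "Site will be included as a fixed variable". No random effect of period is named at either level, and no site-by-period term.

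Table 1 describes an analogous model for the secondary outcomes A1c and LDL. There the test is the interaction between "the treatment group variable and the time period variable at the laboratory measurement level".

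The Sample Size section is written in terms of change. It says that analysing the difference in BP lowers clustering, and that randomizing within site moves between-site variation in BP decline into a stratification factor that the analysis can adjust for. It reports 80% power for 4.4 mmHg with an average of 275 patients per team and two readings per window, "under the most pessimistic assumptions of an ICC of 0.02". Experimental Design Overview and Aims gives five sites, "for a total of 8 intervention and 8 control teams".

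**The concern.** Teams are the randomized units. What threatens the primary test is therefore not that teams differ in BP level but that they differ in how BP changes over the study, for reasons unrelated to the intervention. A team or patient intercept describes level only. It adds the same amount to pre and post readings and so drops out of the pre-post difference. If the model has intercepts and nothing more, the interaction is judged against within-patient reading error from about 4,400 patients (16 x 275), with thousands of degrees of freedom, although only 16 teams were randomized. The statement that the structure accounts for clustering would then be true for BP level but not for the tested term.

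The same applies to site. A site main effect also cancels from the pre-post difference, so it cannot adjust for site differences in BP decline, which the Sample Size section counts on.

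At stake is the validity of the primary p-value and confidence interval.

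**Working it through.** **Inputs from the article.** m = 275 patients per team; 8 teams per arm, so 2,200 patients per arm; ICC 0.02; two readings per window; difference 4.4 mmHg; power 0.8. Alpha and the SD of change are not stated. I assume alpha 0.05 two-sided and solve for the SD.

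**Step 1: does 4.4 mmHg include clustering of change?**
- Design effect: DE = 1 + (m - 1) x ICC = 1 + 274 x 0.02 = 6.48.
- Detectable difference = (1.96 + 0.842) x SD x sqrt(2 x DE / 2200). The required SE is 4.4 / 2.802 = 1.57.
- With DE = 6.48: SD = 1.57 / sqrt(12.96 / 2200) = 20.5 mmHg (19.0 with t on 14 df, 18.5 with t on 10 df).
- With DE = 1: SD = 1.57 / sqrt(2 / 2200) = 52 mmHg (48 and 47 with t on 14 and 10 df).

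An SD of change near 50 mmHg is implausible, so the 4.4 mmHg evidently carries a design effect on the pre-post contrast. The figure itself cannot be reproduced exactly because the SD is not given.

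**Step 2: what does an intercept-only model do?** Write a reading as fixed terms + site + team intercept + patient intercept + error. In a team's mean change (post minus pre), site, team intercept and patient intercept all disappear. Only period, the interaction and reading error remain. This is exact in the planning case of two readings in each window. Patients with readings in only one window disturb the cancellation, but they do not bring team variation in change into the error term. At SD 20.5 such a model would imply a detectable difference of 2.802 x 20.5 x sqrt(2 / 2200) = 1.73 mmHg, not 4.4.

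**Step 3: type I error.** Let r be the ICC of change, and let patients in a team share one true change. Each patient with 2 + 2 readings supplies three within-patient contrasts, and team variation in change enters only one of them. Hence

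(true SE / model SE)^2 = [1 + (m - 1) r] / [1 - r + r/3], and actual alpha = 2 x P(Z > 1.96 / SE ratio).

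| ICC of change | DE | SE ratio | Type I error |
|---|---|---|---|
| 0 | 1.00 | 1.00 | 5% |
| 0.001 | 1.27 | 1.13 | 8% |
| 0.002 | 1.55 | 1.25 | 12% |
| 0.005 | 2.37 | 1.54 | 20% |
| 0.01 | 3.74 | 1.94 | 31% |
| 0.02 | 6.48 | 2.56 | 44% |

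These figures do not depend on the SD. At ICC 0.02 the model SE is 1 / 2.56 = 39% of the true one.

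**Step 4: checks.** In 3,000 simulated null trials per ICC (16 teams x 275, in five sites), the intercept-only test rejected in 4.8%, 7.5%, 20.9%, 32.0% and 43.6% at ICC 0, 0.001, 0.005, 0.01 and 0.02. A regression of the 16 team mean changes on site and arm, with t on 16 - 5 - 1 = 10 df, rejected in 4.4% to 5.0% throughout. One mixed-model fit on a smaller data set (40 patients per team, ICC 0.02) with patient and team intercepts gave an interaction SE of 1.48, equal to the closed form, against a true SE of 2.00.

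**Step 5: patient-level variation in change.** If patients also differ in true change, and this makes up 30% to 50% of the patient-level variance of change (an assumption), type I error is 8% to 11% at ICC 0, 12% to 16% at 0.001 and 49% to 53% at 0.02.

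**The case against.** The article does not say that the model has random intercepts only. It gives nesting levels and fixed terms and does not list the random effects. A three-level model may well contain a random period coefficient, and a condensed article may leave the covariance structure and the degrees-of-freedom method to the full plan. The Sample Size section discusses clustering of change, and Step 1 shows that its figure includes such clustering. That can be read as evidence that the intended model carries this variance. Further, 0.02 is the plan's upper bound: the article expects ICCs for BP well below it, and lower again for change.

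All of this stands, and it limits the claim. A reader might infer that the primary test will have type I error far above 5%. The documents do not support that, because they neither exclude random period effects nor give an ICC of change, and at 0.001 the inflation is modest. A reader might also infer that the 4.4 mmHg or its power must be restated. That would depend on whether normal or t quantiles were used, which the article does not say.

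The objection does not remove the point. The article goes beyond silence: it gives levels, coding, coefficients and test term, and then states that clustering is handled. An analyst who follows that text would naturally fit intercepts, and for the tested term the statement would then be wrong. The site term, as written, does not do what the Sample Size section asks of it.

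**Conclusion.** The point holds in conditional form. Taken as described, the primary model does not carry team-level clustering of BP change into the interaction test, and this conflicts with a sample size that appears to include it. Under that reading, type I error is about 44% at ICC 0.02, 20% at 0.005, 12% at 0.002 and 8% at 0.001. These values assume two-sided alpha of 0.05, 275 patients in every team, two readings per window and one true change shared by patients within a team. The true ICC of change is unknown and expected to be below 0.02, so the actual inflation could lie anywhere in this range or be small. Because the defect would sit in the primary test and is easily closed, it should be settled before the analysis is run.

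**What to change.** State in the primary model:
- a random period effect at team level (team-by-period) and at patient level, in addition to the intercepts;
- a site-by-period term, so that site differences in BP decline are adjusted for as the Sample Size section intends;
- a small-sample test of the interaction (Kenward-Roger or Satterthwaite), on about 10 degrees of freedom (16 teams - 5 sites - 1). An equivalent choice is to analyse the 16 team mean changes adjusted for site.

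If the full plan already contains these terms, one sentence saying so is enough. The same check applies to the analogous models in Table 1. Separately, confirm whether the 4.4 mmHg was computed with t or normal quantiles.

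The cost is two variance terms, one fixed interaction and a degrees-of-freedom option. Intervals will be wider than from an intercept-only model, in line with what the sample size already assumed.

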### Usual Care

Patients assigned to the usual care groups received standard health care services through their primary care provider. Additionally, at VA sites, providers on usual care teams received reports on each of their diabetic patients who had poor blood pressure control and adherence or intensification issues. The information used to produce the report was available in the medical record, although not in the format provided. No recommendation was given regarding follow-up for patients listed on the report. At KP sites, these reports were not required. Instead, in KP, patients in usual care may have been contacted by clinical pharmacists as part of KP's PHASE (Preventing Heart Attacks and Strokes Everyday) program to outreach to patients at high risk for cardiovascular disease (CVD) events. However, pharmacists working with PHASE receive no training in MI, and do not have access to the MMT or any other IT tools that provide adherence or intensification data. In addition, the PHASE program focuses on brief contacts with patients, as opposed to longer episodes of care to address CVD risk factor values.

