### Intervention

The intervention period was defined as the 14 months in which eligible patients were being identified and offered encounters with the pharmacists. Enrollment of patients occurred during months 1-14. Eligibility for the intervention was determined at the beginning of the 14-month intervention period and again at 3, 6, 9, and 12 months. At the start of each quarter, pharmacists received a list of patients with poor blood pressure control and adherence problems or inadequate medication intensification. The list was randomized within 3 blood pressure strata (> = 160, 150-159, 140-149) to allow outreach to the patients with higher blood pressure levels first. The data were then loaded into the tool used by the pharmacists (MMT) described above. Pharmacists were instructed to contact patients in the order that they appeared on their list. At the end of each quarter, if no attempts had yet been made to contact a patient (i.e., the size of the pharmacist's current patient panel was such that the pharmacist did not have time to contact that individual as well as individuals further down the list), that patient was removed from the pharmacist's list.

Prior to being contacted by the pharmacist, patients at the VA sites were notified via a letter mailed by the study team that a pharmacist would be contacting them to invite them to participate in a new clinical program, a customary VA practice for new projects and programs, and therefore required by the governing IRBs. This letter was not required by the IRB governing the KP sites because patients in KP are accustomed to being contacted by the health plan for clinical outreach.

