#### Initial contact by the pharmacist

After a brief review of the patient's electronic medical record (EMR) and information supplied in the MMT, the pharmacist attempted to contact the patient. Often multiple attempts (e.g., leaving messages, calling back at a more appropriate time) were required before talking to a patient. After describing details of the program, the pharmacist invited the patient to participate. If a patient indicated interest in participating, a phone or in person intake encounter was scheduled. Additionally, after a patient agreed to participate in the intervention, the pharmacist mailed a welcome packet to the patient. The packet included an introduction letter from the pharmacist and educational materials, including instructions for home monitoring and documents to record blood pressures and action plans. Information on the patient's current medications was occasionally also included in the packet.

After five attempts to reach a patient without making any contact whatsoever, the patient was considered unreachable and a note was placed in the EMR stating that the patient was eligible for the program but could not be reached to assess interest in the program. If a patient was reached but declined to participate, a few questions were asked to ascertain the reason(s) for declining and to obtain basic sociodemographic information. Pharmacists also notified providers, via a note in the electronic medical record, when a patient declined to participate in the program.

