We want to be able to describe reasons for the diminution or failure of the intervention to reduce blood pressure relative to effect sizes seen in the prior efficacy studies, particularly if those factors are amenable to changes in protocol that could ameliorate their impact. While it is possible that a successful intervention will show persistence of effect into the 6 month post-intervention window, it is possible that we will lose some power to detect an effect by sample loss if patients do not have recorded blood pressures during that period. Furthermore, some patients will have received the intervention early in the course of the intervention period and thus may be as much as 1 year out from the intervention when the 6 month post-intervention period ends and would have become eligible for repeat enrollment and improvement in the blood pressure if the intervention were an ongoing program at the site.

Therefore, a secondary analysis will examine the blood pressure slope starting at the point where patients are activated (initiation of contact for the intervention). Blood pressure changes will be looked at as a function of time after activation. As the activation is determined by random sampling from the list of eligible cases (within systolic blood pressure groups), the entire control group can be used for comparison with their activation date being randomly assigned during the quarter in which the controls meeting eligibility criteria are identified. We will compare the amount of decrease in blood pressure between the intervention and control groups in both the first and second 3 month periods following activation.

A second reason for lack of effect may be that substantial numbers of patients are not willing to participate in the intervention. It is important to quantify this rate of refusal, as well as to try to estimate the effect of the intervention among compliers so that we can assess whether our intervention achieved similar benefits to prior studies among comparable populations of compliers. A naive as-treated analysis is clearly flawed as the comparability between intervention and control groups is lost when we only analyze those patients in the intervention who accepted the intervention. Thus we will carry out a complier average causal effect (CACE) analysis in which the randomization is used as an instrument to estimate the effect of the intervention among the complier population in both the intervention and control group [43].

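### The CACE analysis assumes that assignment does nothing for non-participants, but the design gives them or their providers arm-specific inputs, so the complier effect may be biased in either direction

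*Protocol article*

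**What the plan says.** The section on design issues for analysis rejects an as-treated comparison and plans instead a "complier average causal effect (CACE) analysis in which the randomization is used as an instrument". Its purpose is given there: "so that we can assess whether our intervention achieved similar benefits to prior studies among comparable populations of compliers". The same section keeps patients who were not reached or did not enrol in the primary analysis set.

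Other sections describe what reaches these non-participants or their providers:

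- **Refusers, intervention teams** (Initial contact by the pharmacist): "Pharmacists also notified providers, via a note in the electronic medical record, when a patient declined to participate in the program".
- **Unreachable patients, intervention teams** (same section): after five failed attempts "the patient was considered unreachable and a note was placed in the EMR stating that the patient was eligible for the program"; the note adds that interest could not be assessed.
- **VA letter** (Intervention): before any call, "patients at the VA sites were notified via a letter mailed by the study team that a pharmacist would be contacting them".
- **Team level** (Experimental Design Overview and Aims): one reason for randomizing teams is "to evaluate the real-world effectiveness of pharmacist-team interactions rather than just the efficacy of pharmacist interactions with selected patients"; the other is to limit contamination.
- **VA control teams** (Usual Care): "providers on usual care teams received reports on each of their diabetic patients who had poor blood pressure control" together with adherence or intensification problems. The reports were not required at KP, where usual care patients might instead be contacted under the PHASE program. The design overview calls usual care enhanced by provider information without limiting this to VA; the working below follows the more specific Usual Care section.

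**The concern.** With randomization as the instrument, the arm difference is divided by the participation share. This gives the effect among compliers only if assignment changes nothing for those who would not take part (the exclusion restriction). Any effect of assignment on their blood pressure is credited to, or deducted from, the compliers.

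Here non-participants may be managed differently by arm, because their providers receive different information and, at VA, because intervention patients receive a letter. The imbalance also differs by health system, since control-arm reports belong to VA.

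At stake is the explanatory conclusion. If the main effect is small, the CACE is meant to show whether participants gained as much as in earlier efficacy trials. A biased value could wrongly suggest that delivery matched those trials or fell short of them.

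**Working it through.** **Inputs.** Document: 8 + 8 teams; 275 patients per team, ICC 0.02, detectable difference 4.4 mmHg at power 0.8 (Sample Size). Not given: participation share p, effect of assignment on non-participants d, SD of change, alpha. The article states no CACE figure to reproduce.

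**Plan's own figure.** The design effect is 1 + 274 × 0.02 = 6.48, so the effective size per arm is 8 × 275 / 6.48 = 339.5. At two-sided 5% (assumed), 4.4 = 2.80 × SD × √(2/339.5) gives SD ≈ 20.5 mmHg. The figure is plausible but cannot be verified. The implied standard error of the main contrast is 4.4 / 2.80 ≈ 1.6 mmHg.

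**Bias formula.** Count effects as extra SBP reduction in the intervention arm. Let c be the complier effect against the control care actually given, and assume control patients have no access to the program. Then

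ITT = p·c + (1−p)·d, so ITT/p = c + d·(1−p)/p.

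The bias is zero only if d = 0 or p = 1. The last column takes ITT = 4.4 mmHg for illustration and shows the complier effect, ITT/p − d(1−p)/p, as d runs from +1 to −1.

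| p (assumed) | (1−p)/p = bias per 1 mmHg of d | ITT/p | Complier effect, d = +1 to −1 |
|---|---|---|---|
| 0.3 | 2.33 | 14.67 | 12.33 to 17.00 |
| 0.5 | 1.00 | 8.80 | 7.80 to 9.80 |
| 0.7 | 0.43 | 6.29 | 5.86 to 6.71 |
| 0.9 | 0.11 | 4.89 | 4.78 to 5.00 |

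As a share of the estimate, the bias is d(1−p)/ITT. With d = 1 and p = 0.5 this is 0.5/4.4 = 11%. With an assumed ITT of 2 mmHg it is 0.5/2 = 25%. The distortion is relatively largest when the main effect is small, which is when the CACE would be consulted.

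**Direction.** Take p = 0.5 and a complier effect of 8 mmHg against an untouched control (illustrative; a simulation gave the same values).

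- Notes lower SBP by 1 in non-participants only: (4 + 0.5)/0.5 = 9, against a true 8. Overstated by 1.
- Reports lower SBP by 1 in all controls only: (4 − 1)/0.5 = 6, against a true 7. Understated by 1.
- Both: (4 + 0.5 − 1)/0.5 = 7, against a true 7. They cancel.

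Cancellation needs equal effects. It is possible at VA, but cannot be relied on at KP, where reports were not required.

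**The case against.** A reader might infer that the CACE is shown to be biased. The article does not support that: it gives neither d nor p. Its Background points to a small d. It reports that prompting physicians has had minimal effect, and that preliminary evidence shows no gain in adherence or reduction in clinical inertia from giving them this information alone. The unreachable note carries little content, and the VA reports repeated information already in the record, with no recommendation. All of this stands.

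The team channel can also be over-read. Team randomization was meant to limit contamination too, and the Sample Size section describes pharmacist-provider trust around adjustments the pharmacist makes, hence around treated patients. Spill-over to refusers is possible but not described.

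PHASE contact in usual care might be taken as a further violation. It mainly defines the comparator, as the VA reports do for compliers. That limits comparison with earlier trials but is not in itself a breach of the exclusion restriction. Nor is an effect on non-participants always magnified: the bias exceeds d only when p is below 0.5.

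Finally, this is a condensed article, and the full analysis plan may state the assumption. Its absence is therefore not the point. The point is that the chosen instrument sits uneasily with delivery features the article itself describes. Wording elsewhere could acknowledge and bound those features but not remove them.

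**Conclusion.** The concern holds as a risk of bias, not as a demonstrated bias. The exclusion restriction is doubtful on the article's own description, most clearly because of the intervention-only notes on refusers and unreachable patients. The CACE may be off in either direction by d(1−p)/p: from 2.3 mmHg per 1 mmHg of d at p = 0.3 down to 0.11 at p = 0.9. Both d and p are assumptions; d may be small, and note and report effects may partly offset at VA.

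Only this secondary, explanatory analysis and its comparison with efficacy trials are affected. The primary intention-to-treat comparison stands.

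It is tempting to estimate d from intervention-team patients dropped from the list without an attempt, since lists were in random order within SBP strata. This does not work well. Such patients generate no refusal or unreachable notes, so the clearest channel is missed. Higher strata were worked first, and eligibility was redrawn quarterly, so a dropped patient could be relisted and treated. The main contrast already has an implied standard error of about 1.6 mmHg, so a subset could not resolve a d of about 1 mmHg.

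**What to change.** Keep the CACE as a secondary analysis, with these changes:

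1. State that it assumes no effect of assignment on non-participants, and that this is doubtful here because of the notes, the VA letter, possible team spill-over and the VA control reports.
2. Report ITT/p − d(1−p)/p over a range of d fixed in advance, for example −1 to +1 mmHg (an assumption), using the observed p, overall and separately for VA and KP.
3. Limit the comparison with earlier efficacy trials to that range, and note that the comparator is enhanced usual care.
4. Treat any comparison of unattempted list patients with controls as exploratory at most.

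The cost is analysis-plan wording and a simple calculation on data already collected. The downside is a less definite complier estimate. The system-specific results will be imprecise: with one or two teams per arm at each site, KP's two sites contribute only two to four teams per arm. Patient management and the primary analysis do not change.
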